Whilst there have been a variety of published intervention studies with youths with type 1 diabetes, there are limitations with this work. For example, interventions have not been based on behavioural change theories [10, 18], have uncontrolled designs [19, 20], or consist of a very structured supervised intervention design (e.g. using supervised structured exercise classes in the intervention) [20–24]. Whilst short-term changes in PA might be evident with such supervised settings, often, the PA behaviour reverts back to pre-intervention levels when the supervised intervention is removed [25]. No study has been conducted, to our knowledge, which is theoretically based, adopts a randomised controlled design and has been tailored to young people and families with type 1 diabetes to support long-term lifestyle behaviour change. As such, there is a need for new, higher quality (evidence informed and theoretically based) interventions, which are developed using the UK Medical Research Council (MRC) framework [26].

The MRC framework for evaluating complex interventions will be used as the basis for this research [26]. The framework strongly advises carrying out feasibility and pilot work prior to running a full-scale trial; therefore, in keeping with phases 1 and 2 of the MRC framework, this study proposes to examine the feasibility of recruitment, retention and acceptability of an RCT PA intervention for youths with type 1 diabetes (see Fig. 1). This study aims to (1) develop a theoretically based tailored lifestyle intervention (ActivPals programme) to support active lifestyles for youths with type 1 diabetes and to (2) explore the feasibility of delivering this intervention. The ActivPals programme is being developed from previous work with youths with type 1 diabetes, which highlighted the importance of peer and parental support when leading an active lifestyle. This work will provide critical information for the development of a definitive trial, in addition to providing important information for improving clinical care of type 1 diabetes in youths. The intervention consists of two key phases:

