**Fig. 1 Fig1:**
[figure not shown]
MRC framework for designing and evaluating complex interventions

Phase 1 specific objectives are to develop:An intervention (ActivPals programme) to support active lifestyles in youths with type 1 diabetesFeasible recruitment pathways towards the intervention

Importantly, the intervention and recruitment pathways will be evidence based whilst being pragmatic and suitable for integration within current type 1 diabetes NHS practice.

Phase 2 specific objectives are to recruit participants and conduct a pilot and feasibility trial to determine:The recruitment, initial retention and adherence level that can be achieved for a 4-week intervention programme in both the intervention and control groups.Preliminary evidence of effects of the intervention on physical activity, sedentary behaviour and quality of life. This will provide a preliminary indication of whether the intervention can show change within this group. Following this, an effect size will be estimated for a ‘definitive’ randomised controlled trial.The acceptability of the intervention recruitment pathways and intervention content, delivery, duration and intensity to participants and health professionals.

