#### Feasibility outcome measures

We will monitor the feasibility of the trial by tracking recruitment, retention and adherence rates of participants and the most effective points of recruitment. In addition, feedback about the delivery of the intervention, intervention content and perceived impact will all be explored through the qualitative interviews with participants and parents, carried out at the end of the study. The researchers will also meet with the steering group at the end of the study to feedback the results and discuss intervention acceptability.

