#### Patient-centred outcome measures

Objective measures of physical activity and sedentary behaviour will be collected using the Actigraph GT3X+ monitor. This monitor will allow objective recording of daily time spent in sedentary, light and moderate to vigorous physical activity. These monitors are small (approx size of a 2-pound coin) and lightweight (19 g). Participants will be asked to wear the accelerometers around the waist during waking hours for 7 days, excluding water-based activities. Accelerometer data will be downloaded to Actilife software (version 6.4.3). In line with previous studies, a minimum wear time for a valid day will be defined as 6 h/day, with 3 days of data required for analysis inclusion [33, 34].

The primary outcome measure of daily time spent in MVPA and sedentary behaviour will be determined using cut-points calibrated and validated in paediatric studies: sedentary (<100 cpm) [35] and MVPA (≥3200 cpm) [36]. In addition to the accelerometer data, information will be gathered about the type, frequency and location (e.g. school) of activities undertaken in the last 7 days. This information will be collected from participants with the help of their parent/cares at baseline and follow-up (post-intervention/control). This questionnaire will be developed based on the findings of a previously conducted survey study [37].

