We will also determine key process-related outcomes including intervention recruitment, retention and compliance. As mentioned, a qualitative interview will be carried out post-intervention to determine contextual factors associated with delivery of the intervention and to explore patient and health professional experiences of the ActivPals programme including acceptability of procedures, perceived benefits and difficulties. According to the MRC framework [41], qualitative research can be valuable for identifying what the important or ‘active ingredients’ of an intervention are and which elements are not related to the ‘treatment effect’. Topics which will be covered include perceptions of project, sport and PA participation, views on intervention components, attitudes towards PA, benefits and barriers towards PA and sustainability of PA. A parent is encouraged to participate in the interview. With the participant’s permission, the interviews will be recorded and transcribed. Otherwise, notes taken during the interview will be written up in detail as soon as possible afterwards. Interviews will be analysed by thematic analysis. Feasibility and acceptability measures will be reported including programme implementation and fidelity to protocol.

The measures will give an indication of the effects of the intervention on PA levels, sedentary behaviour and quality of life. The acceptability of the measures and missing data will be considered when designing the full-scale trial.

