### Statistics and data analysis

Descriptive statistics will be presented (mean and standard deviation) with 95 % confidence intervals presented for each group separately. Changes in physical activity and QoL from baseline and follow-up will be assessed using an ANOVA. As this is a feasibility and pilot study, the study will be underpowered; therefore, quantitative outcomes will be interpreted only as feasibility and pilot data.

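### The only outcome labelled primary is MVPA and sedentary time, although the stated question is feasibility, and effects go to an underpowered ANOVA with intervals per group only

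*Protocol article*

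**What the plan says.** **The question.** The Background states that "this study proposes to examine the feasibility of recruitment, retention and acceptability of an RCT PA intervention for youths with type 1 diabetes". The first Phase 2 objective is to determine "The recruitment, initial retention and adherence level that can be achieved for a 4-week intervention programme in both the intervention and control groups". The second seeks only "Preliminary evidence of effects of the intervention on physical activity, sedentary behaviour and quality of life". The third concerns acceptability.

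**The outcomes.** The section on feasibility outcome measures comes first: "We will monitor the feasibility of the trial by tracking recruitment, retention and adherence rates of participants and the most effective points of recruitment". The section on patient-centred outcome measures then contains the only primary label in the article: "The primary outcome measure of daily time spent in MVPA and sedentary behaviour". Later in that section, after quality of life, comes this sentence: "We will also determine key process-related outcomes including intervention recruitment, retention and compliance". It also provides for thematic analysis of the interviews and for reporting of feasibility and acceptability.

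**The analysis.** Under Statistics and data analysis, means and standard deviations are promised with 95% intervals for the two groups separately, followed by: "Changes in physical activity and QoL from baseline and follow-up will be assessed using an ANOVA". The same paragraph concedes that the study is underpowered and restricts the quantitative outcomes to a pilot reading.

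**The concern.** A primary outcome tells the reader which result answers the study question. Here the label sits on activity measures, while the aims are about whether a trial can be run. The label also covers two quantities, MVPA and sedentary time, without saying which leads. The Pilot procedures section refers to a section on primary and secondary outcome measures, but no section carries that heading, so the ranking is not settled elsewhere.

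The second issue is the analysis of effects. The Phase 2 objective is to give a preliminary indication of effect. A randomised comparison does that through the difference between arms and its uncertainty. The statistics section offers intervals within each group, which do not estimate that difference, and an ANOVA, which is ordinarily read through its F test. It does not name sedentary time, half of the outcome labelled primary, unless physical activity is meant to include it.

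At stake is clarity about what the pilot set out to show, and whether the effect data are reported in a form that the planners of a definitive trial can use.

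**Working it through.** **No figure to reproduce.** The article gives 20 participants (Abstract) but no significance level, power, effect size, standard deviation or allocation ratio. I assume 1:1 allocation (n = 10 per arm), two-sided 5% and no dropout. Effects (d) are in units of the SD of change, taken as equal in both arms.

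**Power of the ANOVA.** With two arms and two time points, the ANOVA comparison of change between arms is equivalent to a two-sample t-test (F = t²). The degrees of freedom are 2n − 2 = 18 and the non-centrality is d × √(n/2).
- d = 0.5: 0.5 × √5 = 1.12, power 18%.
- d = 0.8: 0.8 × √5 = 1.79, power 40%.
- d = 1.0: 1.0 × √5 = 2.24, power 56%.
- Effect detectable with 80% power: d = 1.32.

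For comparison, 80% power needs 63 per arm at d = 0.5 and 25 per arm at d = 0.8 (normal approximation). The article's word underpowered is right for all but very large effects.

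**Precision of the between-arm difference.** Half-width = t(0.975, 18) × √(2/10) = 2.101 × 0.447 = 0.94 SD. An observed difference of 0.5 SD would thus be reported as −0.44 to 1.44 SD. If 8 per arm were analysed (20% loss, assumed), the half-width is 2.145 × √(2/8) = 1.07 SD.

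**Precision of the feasibility proportions.** Exact (Clopper-Pearson) 95% intervals. The counts are illustrative, not taken from the article.

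| Count | Proportion | 95% interval |
|---|---|---|
| 18/20 | 90% | 68% to 99% |
| 16/20 | 80% | 56% to 94% |
| 14/20 | 70% | 46% to 88% |
| 8/10 (one arm) | 80% | 44% to 97% |

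These intervals are wide too, but they bear directly on the first Phase 2 objective. Recruitment proportions have a different denominator (those invited), which the article does not give.

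**The case against.** The case for leaving the text alone is substantial.

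- **Two classes of outcome.** The article announces feasibility and patient-centred outcomes as two classes, and feasibility comes first. The primary label appears inside the second class and could mean primary among the patient-centred measures. The word also, in the sentence on process outcomes, need not demote them, since that sentence calls them key. This reading is possible, but the text does not state it, and no outcome outside that class is called primary.
- **Safeguard on interpretation.** A reader might infer that an underpowered test will be the headline result or will decide whether to go on to a full trial. The documents do not support that. No section gives the ANOVA such a role, the statistics section limits quantitative results to a pilot reading, and the list of Phase 2 outputs under Strengths of the research puts recruitment, retention and adherence first.
- **Feasibility is provided for.** A reader might also infer that feasibility has no analysis, or that rates will appear as bare percentages. That goes too far. Rates are tracked, returned slips are counted by source (Appendix), interviews receive thematic analysis, and reporting is promised. How to put an interval on a retention rate is detail that an article may leave to a fuller document.

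All of this limits the harm. It does not remove the conflict between label and aims, or make the stated effect analysis suit its purpose.

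**Conclusion.** The point holds as a mismatch of labelling, plus an effect analysis that can be improved at little cost. The sole primary label covers two activity quantities while the stated question is feasibility. Effects are assessed by an ANOVA with about 18% power at 0.5 SD and 40% at 0.8 SD, with intervals per group only and sedentary time not named. The power figures assume 10 per arm, two-sided 5% and no dropout; any loss makes them worse. The practical consequence is modest because the article already bars a confirmatory reading. Estimating the between-arm difference with its interval of about ±0.94 SD serves the preliminary-effect objective better than a test the plan concedes it cannot power.

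**What to change.** Recruitment is complete, so make this a dated change before analysis.

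1. In the section on patient-centred outcome measures, remove the primary label from the activity measures. Name recruitment, retention and adherence as the primary (feasibility) outcomes, and daily MVPA and daily sedentary time as two separate secondary outcomes. Acceptability stays with the thematic analysis.
2. Under Statistics and data analysis, replace the ANOVA significance test with between-arm differences in change for MVPA, sedentary time and quality of life, each with a 95% interval. Keep the existing pilot-only restriction.
3. In the same section, add that feasibility proportions will be given with 95% intervals.

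The cost is a few sentences and some simple intervals, with no extra participants or measurements. The downside is that the activity result loses its primary label.

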#### Timing

Outcome measures will be assessed at baseline (before intervention) and 1 month after the initial physical activity consultation appointment.

This pilot RCT will be performed according to the Research Governance Framework for Health and Community Care (second edition, 2006).

### Statistics and data analysis

Descriptive statistics will be presented (mean and standard deviation) with 95 % confidence intervals presented for each group separately. Changes in physical activity and QoL from baseline and follow-up will be assessed using an ANOVA. As this is a feasibility and pilot study, the study will be underpowered; therefore, quantitative outcomes will be interpreted only as feasibility and pilot data.

## Discussion

This paper describes the ActivPals study aims and design, including information about the intervention, the outcome measures and recruitment process. Whilst there is a strong evidence base which suggests that regular PA can have a range of physical and psychological benefits for youths with type 1 diabetes, an evidence gap exists between the need to promote long-term lifestyle physical activity in type 1 diabetes care and lack of understanding on how to do this. A vital first step in developing this field is development and piloting a theoretically based, pragmatic, lifestyle intervention for youths with type 1 diabetes.

### Limitations of the research

As this is a small-scale pilot and feasibility study, the researcher (first author) will be recruiting participants, collecting the data and also delivering the intervention. Whilst we acknowledge that a double-blind pilot RCT would strengthen the design of the study, there is limited time and resource with this small-scale pilot study. Therefore, any future funding applications to test the effectiveness of the intervention would include costs for a health professional and research assistant to avoid potential biases in the trial design. Researcher bias will be reduced in the qualitative element of the study as an MSc student, independent to the study, will be conducting the interviews.

The time and funding limitations also restrict the possibility of collecting post-intervention/control follow-up data. Thus, it is not possible to assess long-term effects of the intervention in this small pilot study. These limitations will be addressed in the next phase of work.

### Perceived risk

As the aim of the intervention is to increase physical activity levels, changes to lifestyle are encouraged. There is unlikely to be any pain or discomfort associated with increased physical activity. Participants will be advised to carry out prescribed stretches before and after the activity to minimise any muscle stiffness resulting from exercise. These will be described in detail by the researcher when delivering the intervention. Increased exercise can cause hypoglycaemia in those with type 1 diabetes, if they are experiencing low blood sugar levels. Participants will therefore be asked to monitor blood sugar levels before and during exercising, and post exercise, to minimise the risk of this occurring. Participants will follow Greater Glasgow and Clyde children’s diabetes service exercise guidelines, which will be included in the intervention information books for parents and young people with type 1 diabetes (intervention resources). The researcher will talk participants through this information during the PA consultation. The intervention will be individualised to each participant’s baseline level of activity; therefore, the activity will begin at a level that is comfortable and achievable. Activity intensity, frequency and duration will increase progressively over time. The intervention will be designed by experts working in the physical activity and diabetes field who have experience of advising on appropriate levels and intensity of activity. At the end of the study, the resources will be integrated with current routine care for type 1diabetes (i.e. these will be offered to all patients when they are visiting clinic). Participants will also be given information about support networks and other diabetes care team members they can speak to about increasing physical activity.

### Strengths of the research

A key strength of this study is that it aligns with the development and feasibility stage of the MRC framework for the development of complex health interventions. The findings from this feasibility and pilot study will generate output critical to the subsequent stage of the MRC framework which is the development and running of a definitive trial exploring the effectiveness of physical activity and sedentary behaviour intervention within type 1 diabetes care (see Fig. 1). Specific output from phase 1 will be a new evidence-based, pragmatic and user-informed intervention and suitable recruitment pathways to support active lifestyles for youths with type 1 diabetes. Specific output from phase 2 will be an important information on recruitment, initial retention and the adherence level that can be achieved for a 4-week intervention in both the intervention and control groups. In addition, indicative effect of the intervention on physical activity and sedentary behaviour will be important for the definitive trial. Acceptability of the intervention, recruitment pathways and intervention content, delivery, duration, intensity to participants and health professionals will also be explored. The study will therefore lead to new knowledge of direct relevance to the NHS for improving physical activity both in diabetes care and in the care of youths with other chronic conditions. Importantly, the qualitative interviews will provide information about context of young people with type 1 diabetes lives and will also allow us to understand experiences, attitudes, perceptions and behaviours following completion of the ActivPals PA intervention. This exploratory work will be instrumental in designing and developing a full-scale trial to test the effectiveness of the intervention.

The study is currently under way. All participants were recruited from January to March 2016. Results of the study will be submitted for publication from January 2017.

## Appendix

### Recruitment strategy framework

Stage 1—pool

- Identify target group within population or setting
  Young people aged 7–16 with type 1 diabetes registered at Greater Glasgow & Clyde Paediatric diabetes service.
- Formative evaluation of recruitment approaches
  A multipoint recruitment strategy will be used to recruit from three main sources:
  - GG & C paediatric diabetes clinics (main recruitment site)
  - New start (newly diagnosed) groups or support groups or clubs for young people with type 1 diabetes
  - Screen medical records of paediatric patients registered at the clinic for eligibility to participate in the study

Stage 2—invited

- Offer invitation (January 2016–March 2016)
  Information packs will be given out/sent to the paediatric diabetes service and support groups by the research associate (RA). These will contain a letter introducing the study and information sheets for:
  - Children aged 7–11
  - Young people aged 12–16
  - A relative/parent
  If participants would like to be contacted by the RA with more information about the study, they are invited to sign and return the tear-off slip in the self-addressed envelope provided.
- Monitor response uptake (January 2016–March 2016)
  As monitoring the responses allows the researchers to evaluate the effectiveness of the recruitment strategy (Foster et al., 2011), the RA will monitor how many tear slips are returned and where the participants were recruited from. This will allow the team to asses to most effective recruitment point.
  Telephone reminders have been identified as an effective strategy for recruitment (Treweek et al., 2010); therefore, the researcher will phone participants who have not returned their tear-off slip within a 2-week period. This active method will serve as a reminder to participants and facilitate awareness of the study. Participants can inform the researcher if they want more information about the study or if they do not want to take part in the study. If the information pack has been lost, the researcher will send out another information pack.
  Once all of the participant slips have either returned forms or have confirmed to the research secretary that they do not want to take part in the study, the research team will review the number of consenting participants and assess the success of the recruitment strategy.

Stage 3—responded (January 2016–March 2016)

Participants who requested more information about the study will be contacted by the RA to agree a date and time for a home visit. This date/time will also be agreed with a parent or nominated carer to ensure they also receive information about the study.

- Re-invitation to responders before intervention begins
  Foster et al. (2011) suggest that recruitment and retention to PA studies can be strengthened if participants are invited to participate face to face. Thus, the RA will visit each interested participant in their home (or alternative venue if preferred by participant) to provide more information about the study. Consent forms will also be given to the participants and parent/carer. Consent forms can either be filled in whilst the RA is present or these can be left with participants to allow them time to consider their participation. If the participant is 11 years or younger, a parent/carer must provide consent on the young persons’ behalf, agreeing that they will support the participant to take part in the programme. There will also be an opportunity for participants, parent and carers to ask questions pants about the study.
- Facilitate attendance
  Evidence suggests that greater contact between trial advisors and recruiting sites may increase recruitment (Liénard 2006; Monaghan 2007). Therefore, the researcher will carry out follow-up phone calls to interested participants. These will also act as reminders to participants, parents/carers who have not returned consent forms. Participants will also be encouraged to contact the research team (or an identified colleague independent of the research team) with any other queries.
- Establish eligibility
  - Seven to 16 years with type 1 diabetes registered at Greater Glasgow and Clyde Paediatric diabetes service.
  - Independently ambulatory
  - Are able to undertake physical activity (i.e. have not been advised against doing more PA)
  - Do not have a severe learning disability (and therefore unable to understand the study protocol)
  - Do not have severe challenging behaviour or other needs requiring constant one to one support
- Screen participants
  Participants will we be screened for eligibility based on the inclusion/exclusion criteria.
- Check all consent has been obtained
  The RA will monitor and follow up consent forms. The chief investigator will ensure informed consent is obtained before any of the specific protocol procedures are carried out.
- Baseline measurements carried out
- Randomisation into intervention group/offer starting date (January 2016)
  Participants will be randomised into the ActivPals intervention group or the waiting control group.

Stage 4—intervention begins (February 2016–April 2016)
